## Background

Consumer habits and working conditions strongly influence each member of society’s lifestyle. Smoking, low physical activity and obesity lead to increased individual health risks, e.g., for cardiovascular diseases, cancer, diabetes mellitus, musculoskeletal diseases, etc., putting a very high financial burden on the healthcare system. Recommendations have been made globally and programs developed to support a healthy lifestyle [1–3]. The earlier a healthy lifestyle is implemented, the less likely one is to suffer from the consequences of tobacco consumption, low physical activity, or obesity. However, lifestyle changes are particularly hard to realize when disease-related burdens are not yet apparent. Moreover, people free of cardiovascular diseases but carrying risks like smoking, hypertension, diabetes mellitus, and obesity who initially took statins or antihypertensive drugs decreased physical activity and increased weight, as Korhonen et al. found in their cohort study with > 41,000 participants [4].

Digital programs promoting primary prevention can play an important role for working-age adults. There are already many commercial and non-commercial online programs to support preventive health behavior, although the variety on offer is immense, as is their quality [5]. Some online programs were tested in randomized-controlled trials, but as their content, duration, and possibilities of interactivity differed, the effectiveness varied widely. However, results show that the more individualized and interactive online interventions are aligned, the stronger are their effects [6–13]. Nevertheless, we must keep in mind that strong interactivity and close ties to a web-based program may also make participants feel overly obliged, which may cause users to quit the program prematurely. Particular motivational and volitional factors for changing health behavior are therefore very important [14, 15]. The content of an E-Coach, its individual usability and degree of interaction, and its technical functionality and design are playing an important role to encourage user’s program adherence and thus a successful change in behavior [14].

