### Research questions and hypothesis

The following questions and hypotheses are being investigated in this study
What effects do the online programs within the three health goals *Losing and Maintaining Weight*, *Increasing Fitness*, and *Smoking Cessation* have on the primary and secondary outcomes variables reported by participants?We assume that we will observe statistically significant improvements with small to medium effect sizes for each program.Will the intervention groups (interactive health programs) in each RCT reveal stronger effects on primary and secondary outcomes in comparison to the control groups (non-interactive health programs)? We will test the hypothesis that the intervention groups’ changes in the primary and secondary outcomes are more positive than the control groups’. Our focus is on long-term effects so we will analyze the change between baseline (t0) and 1 year after the intervention finishes (t3), while short-term effects are part of the secondary analyses. We expect small to medium effect sizes from the comparison between these two groups.Does the intensity of use of health programs have an impact on their effects?The hypothesis we test is that study participants who use their health program more frequently and intensively achieve better outcomes than study participants who use the program less often or less intensively.How satisfied with the programs offered are the study participants in the intervention- and control groups? This question will be examined exploratively in secondary analyses.

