**Primary**^**i**^**and secondary**^**ii**^**Outcomes**							
Weight	IRES [48]/Changes in mean kilogram	**W**^**i**^,F^**ii**^,S^ii^	1	**x**	**x**	**x**	**x**
Physical activity	Physical Activity and Sport Activity Questionnaire (BSA-F 3.0) [51]/Changes in mean score	W^ii^,**F**^**i**^	17	**x**	**x**	**x**	**x**
Smoking abstinence in the last 30 days	Self –developed/Changes in percentages (dichotomous data)	**S**^**i**^	1	**x**	**x**	**x**	**x**
Health related goal intention	Goal intention [52] [53]; adapted/Differences of mean values	W^ii^,F^**ii**^,S^ii^	1	**x**	**x**	**x**	**x**
Sport- and movement-related self-concordance	Sport- and movement-related self-concordance [54]/Changes in mean score	F^ii^	12	**x**	**x**	**x**	**x**
Self-efficacy (dietary)	Testing phase-specific self-efficacy [55]/Changes in mean score	W^ii^	7	**x**	**x**	**x**	**x**
Self-efficacy (smoking)	Scales for the measurement of self-efficacy and decisional balance in the process of behavioral change in smokers [56]/Changes in mean score	S^ii^	9	**x**	**x**	**x**	**x**
Barrier management in physical exercise	Barriers and barrier management in physical exercise [57]/Changes in mean score	F^ii^	29	**x**	**x**	**x**	**x**
Expectation of consequences	BRAHMS [50]; adapted/Changes in mean score	W^ii^, S^ii^	18	**x**	**x**	**x**	**x**
Action planning	Action plans and coping plans for physical exercise [58]/Changes in means score	F^ii^	13	**x**	**x**	**x**	**x**
Risk perception	Risk perceptions of cigarettes and e-cigarettes [59]; adapted/Changes in mean score	S^ii^	5	**x**			
Perceived goal attainment	Self-developed/Differences in means	W^ii^,F^ii^,S^ii^	2		**x**	**x**	**x**
Eating behavior German Eating Behavior Scale	German Eating Behavior Scale (SEV)*;article submitted [21]/Changes in mean score	W^ii^, F^ii^	32	**x**	**x**	**x**	**x**
Nicotine dependence	Fagerstrom Tolerance Questionnaire *(*FTND [60])/Changes in mean score	S^ii^	6	**x**	**x**	**x**	**x**
Health-related quality of life	Short Form 12 Health Survey (SF-12) [61]/Changes in mean score	W^ii^,F^ii^,S^ii^	12	**x**	**x**	**x**	**x**

Health goals: W=”Losing and Maintaining Weight”; F=”Increasing Fitness”, S=” Smoking Cessation”

Measurement time point: t0 = baseline, t1 = first follow-up; t2 = second follow-up; t3 = third follow-up; IRES = indicators of rehabilitation status

Primary outcome of the related health goals; highlighted in bold

Secondary outcomes of the related health goals

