Possible covariates (see Table 4) will enter the model at level 1 (X) when they are measured at more than one time point or at level 2 (Z) when they are only measured at baseline. The covariates differ in type and number between the three coaches. The components X and Z are therefore only placeholders. The covariates considered may represent real-life conditions of participants existing independently of the program; they can be beneficial or detrimental to participants’ goal attainment or outcomes. The social environment in particular may be conducive or an obstacle [26–30]. The importance of social and emotional support from people, who are close, is also pointed out by the NICE guideline *Behaviour Change: individual approaches* [31]. Tiredness and a decrease in drive and activity are indications of mood disorders. Self-efficacy, motivation and intention to change, as well as functional or physical limitations are predictors for behavioral change and associated with mental health, health status, and comorbidities [32–40]. Furthermore, it is likely that additional addictive behaviors and low degree of mental health will make smoking cessation more difficult [33, 41, 42]. Since past behavior predicts future behavior, as confirmed in a meta-analysis [43], preconditions such as mental health, health status comorbidity, additional addictive behavior, but also social support, assessed at baseline, are considered as program-independent covariates of primary outcomes. We use these covariates, along with sex, age, and primary outcome at baseline to adjust the statistical models in the analyses. In these models, coefficient *γ*_10_ refers to the change over time of the intervention groups (hypothesis 1), while coefficient *γ*_11_ refers to the difference in change between intervention and control group (hypothesis 2).

For the analyses of secondary outcomes, measuring mean changes over time (see Table 3), we use linear mixed models analogous to the primary outcomes in weight loss and fitness. Differences between intervention and control groups in for example “Health related goal intention” or “Perceived goal attainment” will be analyzed using *t* tests.

To test the dose-effect association (hypothesis 3), the outlined model will be adapted—here, we only use the intervention group, so the group variable will be dropped. Instead of the group variable, a variable that code the use (e.g., number of logins) of the coach will enter the model at level 2.

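### The hypothesis-3 dose model is a non-randomised comparison that leaves out baseline intention and self-efficacy, which the plan itself calls predictors of change and already measures at t0

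*Protocol article*

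**What the plan says.** Under Research questions and hypothesis, the third question is causal in wording: "Does the intensity of use of health programs have an impact on their effects". The hypothesis attached to it is that "study participants who use their health program more frequently and intensively achieve better outcomes" than those who use it less.

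Summative evaluation describes the test. The basic multilevel model is adapted: "here, we only use the intervention group, so the group variable will be dropped", and "a variable that code the use (e.g., number of logins) of the coach will enter the model at level 2".

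The same section justifies the covariates. It states that "Self-efficacy, motivation and intention to change, as well as functional or physical limitations are predictors for behavioral change" and are associated with mental health, health status and comorbidity. It then selects mental health, health status and comorbidity, other addictive behaviour and social support, and concludes: "We use these covariates, along with sex, age, and primary outcome at baseline to adjust the statistical models in the analyses". Table 4, the named source of covariates, contains no intention, self-efficacy or other motivation scale.

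The Background, after noting that users may quit a program early, says: "Particular motivational and volitional factors for changing health behavior are therefore very important".

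Table 3 lists "Health related goal intention" at t0 for all three trials, dietary self-efficacy at t0 for weight, smoking self-efficacy at t0 for smoking, and self-concordance, barrier management and action planning at t0 for fitness. All are there as secondary outcomes. The baseline questionnaire is completed before program access (Randomization).

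**The concern.** Once group is replaced by observed use, randomisation no longer balances the people being compared. Those who log in often differ at entry from those who log in once. Initial motivation is the obvious candidate for a common cause of use and change. The article ties it to change explicitly, and to staying with a program at least by implication in the Background. It is measured before exposure, yet it is not in the adjustment set.

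Leaving it out is harmless for the randomised comparison (hypothesis 2) but not for hypothesis 3. The use coefficient may partly describe who the heavy users are, and the hypothesis could be declared confirmed with no effect of use. The Discussion says the study should inform quality criteria for web-based programs, where a dose claim would carry weight.

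**Working it through.** **1. Where the covariates enter.** In the basic model the intercept equation holds group and the baseline covariates Z. The slope equation is γ10 + γ11·group + u1j. With use substituted for group, the dose effect on change is the use-by-time coefficient, and no covariate stands beside it. Two further points weaken the stated adjustment:

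- PHQ-2 and social support are measured at t0 to t3. Under the level-1 rule they would be centred on each person's own mean, which removes between-person differences. The text also speaks of baseline values, so which applies is unclear.
- In the smoking trial everyone smokes at t0, so the baseline outcome adjusts nothing. Because t0 is dropped there, part of a use effect sits in the intercept, which the listed covariates do adjust.

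**2. Sample sizes.** The article gives no figure for hypothesis 3; its sample-size table only supplies n. For d = 0.25, two-sided 0.05 and power 0.80, the t-test needs 252.13, so 253 per arm, as stated. For 15% versus 2%, 77 per arm gives Fisher exact power 0.801. Randomised per arm: 1114/2 = 557 for fitness and weight; 339/2 = 169.5, taken as 169, for smoking.

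**3. Assumptions (none in the article).** True effect of use is zero. Baseline motivation has correlation r with use and r with true individual change. Intercept variance is 1, slope variance 0.1, residual variance 0.5. Times are coded 0 to 3 as planned, with complete data.

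**4. Closed form for the random-slope model, motivation omitted.**

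- Spurious use-by-time coefficient per SD of use: b = √0.1 × r².
- Variance of one person's estimated slope: 0.1 + 0.5/5 = 0.2, since Σ(t − 1.5)² = 5. Hence SE = √(0.2/n): 0.0281 at n = 253 and 0.0189 at n = 557.
- Example, r = 0.3, n = 253: b = 0.316 × 0.09 = 0.0285; b/SE = 1.01; rejection = 1 − Φ(1.96 − 1.01) + Φ(−1.96 − 1.01) ≈ 17%.

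| r (both) | n = 253, closed form | n = 253, simulated | n = 557, closed form | n = 557, simulated |
|---|---|---|---|---|
| 0.1 | 5% | not run | 5% | not run |
| 0.2 | 7% | 7% | 10% | 11% |
| 0.3 | 17% | 17% | 32% | 31% |
| 0.4 | 44% | 43% | 76% | 75% |

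The simulation used 1,500 runs per cell.

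**5. Simple correlation test as a cross-check.** The spurious correlation is r², tested by Fisher z with z = atanh(r²)·√(n − 3). For r = 0.1, 0.2, 0.3, 0.4:

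- n = 253: 5%, 10%, 30%, 72%
- n = 557: 6%, 16%, 57%, 97%
- Smoking, as a rough linear approximation only: 5%, 6%, 12%, 28% at n = 77 and 5%, 8%, 21%, 55% at n = 169

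These rates are higher because here r refers to observed change. In step 4 it refers to the true slope, and half of the observed slope variance is noise (0.1 of 0.2). Step 4 is closer to the planned model.

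**6. Effect of adjusting.** In the simulation, adding motivation to the intercept only left the rates unchanged at 7%, 17%, 43% (n = 253) and 11%, 31%, 75% (n = 557). Adding motivation and motivation-by-time brought them to about 4% to 5%. That assumes perfect measurement. With an assumed reliability of 0.7, the closed form leaves 5%, 6%, 9% (n = 253) and 6%, 8%, 14% (n = 557) at r = 0.2, 0.3, 0.4.

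**The case against.** The strongest reply is that this is a condensed article. Covariates are called possible, X and Z are placeholders, the hypothesis-3 model is only sketched, and a final list belongs in an analysis plan that is not shown. This carries some weight, but the article does not leave the matter open: it names Table 4 as the source, states which covariates are used, and writes a slope equation without any.

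The health covariates may also act as partial stand-ins for motivation, and sex, age and baseline outcome are adjusted for. That is fair, but in the model as written none of them touches the use-by-time term.

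The article itself calls this a dose-effect association, and the hypothesis, read literally, only says that heavier users do better. That stands too. Only the research question asks about impact, so the wording needs aligning rather than reversing.

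A reader might infer more than the article supports:

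- That motivated users will certainly produce a dose effect. This requires motivation to be related to both use and change. Neither correlation is given, and if either is near zero the bias is negligible.
- That the plan names planning as a predictor of change. Its list is self-efficacy, motivation, intention and functional or physical limitations. The nearest support is the reference to volitional factors in the Background, and action planning is measured in fitness only.
- That the trials' main result is affected. Hypothesis 2 and the sample sizes are not.

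**Conclusion.** The point holds in a limited form. As written, the dose model is a within-arm observational comparison that leaves a named and measured potential confounder uncontrolled, and its slope equation adjusts for nothing.

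The size is illustrative because it rests on assumed correlations and variance components. The false-positive rate is near the nominal 5% when both correlations are 0.1. In the random-slope model it is about 7%, 17% and 43% at 0.2, 0.3 and 0.4 with 253 participants, and 11%, 31% and 75% with 557. The rough smoking figures at 77 completers are smaller. The consequence is confined to what hypothesis 3 may conclude.

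**What to change.** In the hypothesis-3 model:

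- Add t0 goal intention in all three trials, t0 self-efficacy in weight and smoking, and the t0 motivational and volitional scales in fitness (self-concordance, barrier management, action planning).
- Enter each as a main effect and with its time interaction; a main effect alone does not correct the use-by-time term. Give the covariates already listed a time interaction as well where the sample allows.
- Use t0 values only, because later values may lie on the path from use to outcome.
- Report the use coefficient with and without these terms, and state the result as an association adjusted for baseline motivation, not as an impact. The same wording should govern the comparison of one-time and repeated users under Sensitivity analysis and missing values.
- In smoking, limit the additions to goal intention and self-efficacy: 15% of 77 completers is 11.55, about 12 abstainers.

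Cost: a few degrees of freedom in one secondary model and no new data. The smoking model is already crowded for so few events, so its adjusted estimate will be imprecise. Goal intention is a single item, so some residual confounding will remain and should be acknowledged.

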### Study outcomes and data analyses

#### Summative evaluation

Our four major research questions for this project are illustrated above.

We will use a linear mixed model (LMM) for the primary outcomes weight loss (kilogram) and fitness (BSA-Score), and for the outcome smoking cessation, we use a generalized linear model (GLMM) because of the dichotomous outcome variable (Smoking yes/no). The cluster variable is the person-id (level 2-group variable) with the time point nested within it (level 1 measurement), that permits us to model individual and group level changes [23–25]. For each primary outcome, we apply the following basic model with cross-level interaction and random slopes:

Level 1: *Outcome* = *β*_0*j*_ + *β*_1*j*_ ∗ *time* + *β*_*nj*_ ∗ *X*_*nj*_ + *r*_*ij*_

Level 2: *β*_0*j*_ = *γ*_00_ + *γ*_01_ ∗ *group* + *γ*_0*n*_ ∗ *Z*_0*n*_ + *u*_*oj*_
$$ {\beta}_{1j}={\gamma}_{10}+{\gamma}_{11}\ast group+{u}_{1j} $$

“Group” will be a dichotomous variable, which contrasts the intervention group vs. the control group. ’Time’ consists of four time points coded with 0 to 3.

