All metric covariates at level 1 will be group mean-centered, while metric covariates at level 2 will be grand mean-centered. Categorical variables enter as dummy-coded (0/1) variables.

Post-hoc analyses with correction for multiple testing will be conducted to identify changes between specific time points to analyze short-term effects, e.g., between t0 and t1. As effect size, with their 95% confidence intervals, we will calculate Cohen’s *d* bases on the *t* values from the pairwise comparisons from the LMM respective odds ratio for the GLMM.

In the case of the *SmokingCessationCoaching*, we will drop the baseline (T0) from the model, because every case concerns smoking. It is, therefore, not possible to calculate the odds ratio for the change between baseline and post-intervention. Instead, we will use the difference in smoking cessation at post intervention between both groups as the effect size.

Furthermore, we will apply structural equation modeling to test various models for assessing potential mediators of the intervention effect on outcomes.

The analyses are carried out according to the intention-to-treat principle (ITT). In ITT, all randomized participants will be considered in the main analyses. In per-protocol analyses (PP), only those participants will be included who have been randomized, have participated at all time points, and filled out corresponding primary outcomes. The randomization condition for study participants was that they accessed the program at least once.

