### Sample size calculation

#### Randomized controlled trials

We calculated the sample size for each randomized controlled trial (RCT) separately (see Table 5) by considering the effect sizes of the primary outcomes in comparable trials [8–11], the α-error (0.05), and the power we were striving for (1 − *β* = 0.80). Our power analyses were done using GPOWER software. While we assumed a general online-RCT dropout rate of 50% [45, 46], we estimate a dropout rate of about 15% in the medical substudies in light of experiences with similar studies involving personal medical examinations. We have accounted for an additional 10% buffer for the online RCTs.

**Table 5 Tab5:** Sample size calculations for the three RCTs including medical substudies

Health goals	“Increasing Fitness“		“Losing and Maintaining Weight”		“Smoking Cessation“
RCTs	Online questionnaire study	Online-questionnaire study + medical substudy:	Online questionnaire study	Online-questionnaire study + medical substudy:	Online questionnaire study
**Primary outcome**	Physical activity (BSA)	questionnaire study: physical activity (BSA); medical examinations: VO_2 max_	Weight loss	Questionnaire study + medical examinations: weight loss	Abstinence from smoking
**Effect assumption for primary outcome**	effect size = 0.25	questionnaire study: effect size = 0.25 ; medical examinations: effect size = 0.45	Effect size = 0.50	Effect size = 0.50	15% in intervention group versus 2% in control group
**Required case-number results** (two-sided, alpha = 0.05, beta = 0.80)	253 (for each intervention group IG and control group CG)^1^	79 (for each IG and CG)^2^	253 (for each IG and CG)^1,3^	64 (for each IG and CG)^2^	77 (for each IG and CG)
**(assumed dropout)** **minimally required sample size**	(50%) 506 (for each IG and CG)	(15%) 93 (for each IG and CG)	(50%) 506 (for each IG and CG)	(15%) 75 (for each IG and CG)	(50%) 154 (for each IG and CG)
**total sample size (IG + CG + ca. 10% buffer for questionnaire study**	(506 + 506) × 1.1 *N* = 1.114	(93 + 93) *N* = 186	(506 + 506) × 1.1 *N* = 1.114	(75 + 75) *N* = 150	(154 + 154) × 1.1 *N* = 339

IG = intervention group (specific online coach for the health goal chosen), CG = control group (specific health information for the health goal chosen)

^1^As we aimed to assess the groups undergoing additional medical exams separately from those only completing the online questionnaire, the former group’s sample size is not included in this calculation

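### Cohen's d taken from mixed-model t values of change contrasts depends on the within-person correlation and the degrees of freedom, so it is not a reliable gauge of small-to-medium effects

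*Protocol article*

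**What the plan says.** The protocol article, under Summative evaluation, plans linear mixed models for weight and for the BSA physical activity score. The measurements are clustered within participants: "The cluster variable is the person-id (level 2-group variable) with the time point nested within it". It then announces: "Post-hoc analyses with correction for multiple testing will be conducted to identify changes between specific time points", giving t0 to t1 as an example. The effect size follows directly: "we will calculate Cohen’s *d* bases on the *t* values from the pairwise comparisons from the LMM". No standard deviation to divide by, no correction for correlation and no rule for degrees of freedom accompanies this.

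The size of the effect is part of what is hypothesised. Under Research questions and hypothesis, the first hypothesis reads "We assume that we will observe statistically significant improvements with small to medium effect sizes for each program", and for the arm comparison the text says "We expect small to medium effect sizes from the comparison between these two groups". Table 5 plans the online trials with effect sizes of 0.25 (physical activity) and 0.50 (weight loss).

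The smoking trial uses an odds ratio or a difference in cessation, so the point concerns only the weight and fitness trials.

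**The concern.** A t value converts to a familiar standardised mean difference when it comes from independent observations and its standard error is built on the between-person SD. In a change contrast, or an arm difference in change, the standard error is built on the SD of change. That SD is small when the outcome tracks closely within a person and large when it does not. A two-level model also allows degrees of freedom to be counted in persons or in observations, and the usual conversion divides by their square root.

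The same programme effect can therefore be reported as quite different values of d. At stake is the reading of the first two hypotheses. The comparison of the weight trial with the fitness trial is also affected: if body weight tracks more closely than a questionnaire score, equal effects in baseline SD units would give unequal d.

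**Working it through.** **Inputs from the article.** Table 5: effect sizes 0.25 and 0.50, two-sided alpha 0.05, power 0.80, 253 per arm for the online trials. Summative evaluation: four visits, clustering by person. **Assumed:** within-person correlation r between 0.3 and 0.95, and equal variance at each visit. The article gives neither.

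**1. The plan's own figures.** A two-sample t test (noncentral t) at d = 0.25 needs 253 per arm, as stated. At d = 0.50 it needs 64 and at d = 0.45 it needs 79, matching the substudy columns. Then 253/0.5 = 506 per arm, and 1012 × 1.1 = 1113.2, printed as 1114. These figures reproduce.

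**2. Arm difference in change.** Let the true difference be D baseline SDs, with n per arm.

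- t = D / [√(2(1−r)) × √(2/n)]
- plain conversion: d = 2t/√df
- person df = 2 × 253 − 2 = 504
- observation df = 4 × 506 − 506 − 6 = 1512

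Example at r = 0.9, D = 0.25: t = 0.25 / (0.447 × 0.0889) = 6.29. Then d = 2 × 6.29/√504 = 0.56, or 2 × 6.29/√1512 = 0.32.

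| r | t | d, person df | d, observation df |
|---|---|---|---|
| 0.3 | 2.38 | 0.21 | 0.12 |
| 0.5 | 2.81 | 0.25 | 0.14 |
| 0.7 | 3.63 | 0.32 | 0.19 |
| 0.8 | 4.45 | 0.40 | 0.23 |
| 0.9 | 6.29 | 0.56 | 0.32 |
| 0.95 | 8.89 | 0.79 | 0.46 |

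With person df the multiplier is essentially 1/√(2(1−r)): below 1 for r under 0.5, above 1 beyond it. A true 0.50 gives 0.42 to 1.58 with person df over the same range.

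**3. Change within one arm (first hypothesis).** For a change of 0.25 SD and n = 253, t = 0.25/√(2(1−r)/253). Then t/√n runs from 0.21 to 0.79, and 2t/√(n−1) from 0.42 to 1.58.

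**4. Dropout.** Table 5 assumes 50% loss. At r = 0.5, with 253 of 506 per arm supplying the information, t = 2.81. Completer df (504) gives 0.25. Counting all randomised persons (1010) gives 2 × 2.81/√1010 = 0.18.

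A small simulation (four visits, random intercept, 506 per arm, 15 replicates per setting) compared no loss with 50% loss:

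| r | df counting all randomised persons | df following observed records |
|---|---|---|
| 0.5 | 0.26 to 0.18 | 0.151 to 0.145 |
| 0.8 | 0.38 to 0.30 | 0.22 to 0.24 |
| 0.95 | 0.80 to 0.57 | 0.46 to 0.47 |

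Dropout thus matters clearly only under the first convention.

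**5. The alternative.** In the same runs, the model contrast expressed in baseline SD units stayed between 0.24 and 0.26 in every setting.

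**The case against.** - **The contrasts need not be within-person.** The text says pairwise, not paired. That is right, but the preceding sentence speaks of changes between time points. If the contrasts were arm differences at one visit, the planned adjustment for the baseline outcome would still tie t to r, by a factor 1/√(1−r²). A true 0.25 would give 0.25/√0.75 = 0.29 at r = 0.5.
- **No formula is given, and a corrected conversion exists.** Multiplying by √(2(1−r)) restores 0.25 in the person-df calculation, and a condensed article may leave the formula to a fuller document. The exact conversion is therefore open. The article does, however, fix t values as the source of d, and a plain conversion is the natural reading.
- **A mismatch with Table 5 is not shown.** A reader might infer that the planned 0.25 and 0.50 are in baseline SD units and that the reported d is on another scale. The sample sizes cannot tell: a two-sample test needs the same n whether the SD is of baseline values or of change. Table 3 describes these outcomes as changes, which leaves SD-of-change units possible. The weight programme aims at no more than 5 kg in 12 weeks, and 0.50 baseline SD would exceed that if the t0 SD were above 5/0.50 = 10 kg. This part of the objection stands.
- **The calculations are not the stated model.** They leave out random slopes, covariates including baseline outcome, and multiple imputation. Random slopes add variance to change and would probably soften the inflation at high r. This also stands: the tables show the mechanism, not a forecast.
- **Unstandardised results are already planned.** Table 3 lists changes in mean kilogram and mean score, and the sensitivity analyses compare raw change. That limits the harm but does not repair d.

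**Conclusion.** The point holds as a recommended improvement. A plain conversion of the t values turns one true arm difference of 0.25 baseline SD into 0.21 to 0.79 (person df) or 0.12 to 0.46 (observation df). This rests on r assumed from 0.3 to 0.95, equal variances, complete data and 253 per arm. A d with that dependence is not a reliable measure of whether effects are small to medium, and should not be compared between the weight and fitness trials.

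Three stronger readings are not supported. The d is not always inflated: with person df it is too small when r is below 0.5. Dropout does not lower it in general. Nor are the tests in doubt: the group-by-time coefficient, its P-value and the sample size are untouched. How large the distortion would be under the full stated model remains unknown.

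**What to change.** Under Summative evaluation, replace the t-to-d conversion. For each contrast (primary: arm difference in change from t0 to t3), divide the model-estimated difference and its 95% confidence limits by one fixed observed SD, the pooled t0 SD of that outcome across both arms. Use the same SD for ITT and per-protocol analyses. Report the unstandardised difference (kg, BSA score) with its confidence interval as the main effect measure.

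State which SD the effect sizes in Table 5 refer to. If they were in SD-of-change units, say so, and also give the contrast divided by the observed SD of change when comparing with Table 5.

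The cost is about one sentence of analysis text, or two with the Table 5 note. No new data are needed, because both outcomes are collected at t0 and the baseline questionnaire is completed before randomisation. The downside is that the standardised weight effect may look smaller than a t-based d.
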